## Methods/Design

### Overall study design

This study will be a randomized controlled trial (RCT) with pregnant women randomly allocated to either the HC Intervention or an Education Alone control group. The study will be conducted and reported in line with CONSORT recommendations [55]. Baseline assessment of study variables will occur at 14-16 weeks gestation; this allows women to consider the pregnancy certain (since the threat of miscarriage has substantially decreased) and to participate at a standardized time point. Follow up assessments will take place at 32 weeks gestation, and at 6 weeks, and 6 and 12 months postpartum. The study was approved by the Eastern Health Human Research Ethics Committee on the 25th March, 2011 (EH-HREC E40/1011) and Deakin University Human Research Ethics Committee on 21st April, 2011 (DUHREC 2011-087).

### Participants

Participants will be 220 pregnant women. Women will be able to participate if they provide informed consent, have a BMI > 18.5 (US IOM cut-off for normal weight), are 18 years of age or older, English speaking and less than 18 weeks gestation at recruitment with no history of disordered eating or diabetes. After baseline assessment, women who meet the eligibility criteria will be randomly allocated to either the HC Intervention group (*n *= 110) or the Education Alone group (*n *= 110). A coded, double-blinded, variable-length permuted blocks randomized treatment allocation schedule, produced by computer algorithm, will be used.

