**Methods/Design:**

The randomized controlled trial will be conducted with 220 women who have a BMI > 18.5 (American IOM cut-off for normal weight), are 18 years of age or older, English speaking, no history of disordered eating or diabetes and are less than 18 weeks gestation at recruitment. Women will be randomly allocated to either a specialized HC intervention group or an Education Alone group. Our specialized HC intervention has two components: (1) one-on-one sessions with a Health Coach, and (2) two by two hour educational group sessions led by a Health Coach. Women in the Education Alone group will receive two by two hour educational group sessions with no HC components. Body Mass Index, waist circumference, and psychological factors including motivation, readiness to change, symptoms of depression and anxiety, and body dissatisfaction will be assessed at baseline (14-16 weeks gestation), and again at follow-up: 32 weeks gestation, 6 weeks, 6 months and 12 months postpartum.

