### Excessive weight gain during pregnancy

Excessive weight gain in pregnancy is a common health-related problem in Western countries [3]. Women who gain excessive weight during pregnancy have an increased risk of postpartum obesity in themselves and their children [2,4]. Furthermore, 20% of women retain at least 5 kg of gestational weight gain at 6-18 months post birth [5,6], and this weight retention is a strong predictor of maternal overweight and obesity a decade or more after birth [7].

In 2009 the United States (US) Institute of Medicine (IOM) published revised guidelines for how much weight a woman should gain during pregnancy and highlighted the importance of intervention in pregnancy to prevent both postpartum weight retention and childhood obesity [8]. The US IOM recommends that women with a normal weight (Body Mass Index, BMI, of 18.5-24.9 kg/m^2^) should gain between 11-16 kg during their pregnancy; women who are overweight (BMI of 25-29.9 kg/m^2^) should gain 7-11 kg, and obese women (BMI of 30 kg/m^2 ^and above) should gain between 5 to 9 kg [8]. Women who are underweight (BMI less than 18.5 kg/m^2^) should gain between 13 to 18 kg during pregnancy [8]. Excessive gestational weight gain (GWG) is defined as weight gain above these recommended guidelines. The specific cost of excessive gestational weight gain is related to ensuing maternal health problems and fetal outcomes [9], such as preeclampsia [10], maternal hyperglycemia [11], complications with labor/delivery [12,13], infant macrosomia [12,13], late fetal death [14], birth defects [15], and an increased risk of caesarean [10].

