The Health Coaching Australia (HCA) Model [49] is an integrated Health Coaching model drawing on evidence-based psychological theories, practices and principles, such as Social Cognitive Theory [51], Readiness to Change, Importance, and Confidence [52], the Transtheoretical Model [53], and the Theory of Planned Behavior [54]. The HCA Model offers a unique intervention approach for preventing excessive gestational weight gain and weight retention in the postpartum because it provides behavioral, cognitive, situational, and emotional change facilitation: not just behavioral change facilitation [49].

We have developed a novel pregnancy HC intervention that has two components. (1) One-on-one sessions with a Health Coach that a) promote women's adoption of healthy lifestyle behaviors for the purpose of weight management, and b) address mood management and body image issues that commonly arise during pregnancy. (2) Educational group sessions, that augment the one-on-one sessions; the aim is to provide new mothers with additional information related to healthy behaviors and mood, and to support and assist them in initiating, maintaining, and achieving their goals for healthy behavior change.

### Specific aim 1

To compare the effectiveness of a specialized HC intervention during pregnancy, in preventing excessive gestational weight gain and postpartum weight retention 12 months post birth, compared to education alone. Hypothesis: In comparison to the education alone group, there will be a significantly greater proportion of women in the intervention group who: (1) will gain weight within the recommendations outlined by the American IOM [8] for gestational weight gain; (2) will have returned to their pre-pregnancy weight by 12 months post birth.

### Specific aim 2

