#### Other relevant variables

Other variables will be included to ensure comprehensive assessment and will be examined as secondary, or covariate variables. These include parity, socioeconomic status, substance use, healthcare resource-use, perceived social support, coping style and appraisal of stressful events, beliefs about gestational weight gain, labor experiences (e.g., length, type), breast-feeding experiences, birth weight and delivery date.

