### Power, sample size, and retention

Given that the primary outcome of the study is maternal BMI, we aim to detect a clinically relevant difference in BMI of 0.8 kg/m^2 ^at 12 months postpartum. This difference is in accordance with the New Life (style) RCT that is currently being conducted in the Netherlands [63], that targets weight advice, weight development, nutrition and physical activity habits, but fails to target motivational variables, behavior-change assistance or psychological factors, such as depressive symptoms, anxiety symptoms, and body image. Consequently, the required *n *to detect this difference with 80% power at *α *= 0.05 and a standard deviation of 2 kg/m^2^, is 110 women per group; we have adopted this SD because we will also be measuring weight objectively at baseline and 12 months postpartum, removing any bias associated with self-report. Allowing for attrition of 20%, we will recruit 264 women and randomly assign 132 women into the HC Intervention and 132 women into the Education Alone control group. Our estimate of a drop-out rate is conservative and based on our previous large longitudinal studies with pregnant women and multiple time points [21,23,64]. As in our previous longitudinal pregnancy studies, this attrition rate of 20% takes into consideration that 5-7% of women may be diagnosed with gestational diabetes, which we expect to occur at 24-26 weeks; these women will therefore not affect the intervention, because we will over sample. A permuted blocks randomized treatment allocation schedule, produced by computer algorithm, will be used for the randomization process. To facilitate retention, we will build rapport with the participants through a study website, a regular newsletter, telephone support and advanced notification of assessments.

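### Entry is not limited to singleton pregnancies, although the only gestational-gain limits stated depend on BMI alone; the effect is small and one eligibility line removes it

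*Protocol article*

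**What the plan says.** The entry criteria appear twice in the protocol article. The Participants section opens with "Women will be able to participate if they provide informed consent, have a BMI > 18.5", adds an age limit of 18 years, and ends with "English speaking and less than 18 weeks gestation at recruitment with no history of disordered eating or diabetes". Women who meet these criteria are then randomised after the baseline assessment. The Methods/Design part of the abstract gives the same list without consent, including "no history of disordered eating or diabetes and are less than 18 weeks gestation at recruitment". Neither place mentions the number of fetuses, and no other section does.

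The Background section on excessive weight gain sets out the IOM ranges: 11-16 kg for normal weight, 7-11 kg for overweight, 5-9 kg for obese and 13-18 kg for underweight women. It then states: "Excessive gestational weight gain (GWG) is defined as weight gain above these recommended guidelines". BMI is the only factor that selects the range.

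Specific aim 1 makes this an endpoint. Part (1) of its hypothesis is that a greater proportion of the coaching group "will gain weight within the recommendations outlined by the American IOM [8] for gestational weight gain".

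The covariates under Other relevant variables include parity and end with "labor experiences (e.g., length, type), breast-feeding experiences, birth weight and delivery date"; number of fetuses is not among them. The Analyses section gives no separate rule for multiple pregnancies and commits to analysing every participant in her allocated condition.

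**The concern.** The population as described and the endpoint as described do not fit each other. A woman carrying twins satisfies every listed criterion. Her total gain includes a second fetus with its placenta and fluid, which is not excess maternal weight, yet the limits in the article make no allowance for it. Some women could be put in the wrong category on part (1) of the aim 1 hypothesis for a reason unrelated to coaching.

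This is hard to repair later. Removing such women after randomisation, without a rule fixed beforehand, would sit badly with the intention-to-treat commitment. Nor do the listed covariates clearly deal with it: birth weight is listed, but how it would be entered for two infants is not stated. The sample-size section does foresee gestational diabetes in 5-7% of women and allows for it by over-sampling; it says nothing about multiple pregnancy, which acts directly on gestational gain.

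What is at stake is the precision and clean interpretation of one binary endpoint, not the validity of the trial.

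**Working it through.** **The plan's own figure.** The only sample-size calculation concerns another outcome: "we aim to detect a clinically relevant difference in BMI of 0.8" kg/m² at 12 months postpartum, with SD 2 kg/m², 80% power and alpha 0.05, giving 110 per group. The usual two-sided normal formula gives 2 × (1.960 + 0.842)² × (2/0.8)² = 98.1, so 99 per group. The stated 110 does not reproduce exactly but is on the safe side (power about 84%). Nothing below depends on it; there is no power calculation for the gain endpoint to reproduce.

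**Inputs for the size of the problem**
- N = 220 (Participants) or 264 (Power, sample size, and retention); 110 per group.
- f = share of multiple pregnancies. The article does not give it. Assumed 1-2%, with 3% as a stress case.

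**Step 1: expected number, N × f**
- 220 × 0.01 = 2.2; 220 × 0.02 = 4.4; 220 × 0.03 = 6.6
- 264 × 0.01 = 2.6; 264 × 0.02 = 5.3; 264 × 0.03 = 7.9

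**Step 2: chance of enrolling at least one, 1 − (1 − f)^N, for N = 220**
- 1%: 89.0%
- 2%: 98.8%
- 3%: 99.9%

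So the case is likely to arise, in very few women.

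**Step 3: average dilution.** Take the worst case, in which every such woman in both arms is scored outside the range. Each within-range proportion is then multiplied by (1 − f), and the difference between groups shrinks by the fraction f. The article gives no proportions, so 40% v 60% is used for illustration, with 110 per group, two-sided alpha 0.05 and the normal approximation with pooled variance under the null:
- f = 0: difference 20.0 points, power 84.8%
- f = 1%: 39.6% v 59.4%, difference 19.8 points, power 84.1%
- f = 2%: 39.2% v 58.8%, difference 19.6 points, power 83.3%
- f = 3%: 38.8% v 58.2%, difference 19.4 points, power 82.6%

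**Step 4: chance imbalance.** If k such women enrol and each is equally likely to enter either arm, the chance that all fall in the same arm (either one) is 2 × 0.5^k. The largest shift in that arm's proportion is k/110.
- k = 3: probability 25%, shift at most 3/110 = 2.7 points
- k = 4: probability 12.5%, shift at most 4/110 = 3.6 points

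These shifts are upper limits: every one of the women must be scored outside the range and must otherwise have been within it.

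**The case against.** Four objections deserve an answer.

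**This is an omission in a condensed article.** The full protocol may contain a singleton criterion, and neither list claims to be exhaustive. That is possible. But the article gives the list twice, as the conditions for taking part, in detail that extends to language and eating history, and randomises women who meet it. The point is that the stated population does not fit the stated endpoint, not that analysis detail is absent. If the full protocol already restricts entry, the remedy is to carry that line into the article.

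**The endpoint refers to the cited guideline, not to the Background summary.** This stands in part. Specific aim 1 cites the IOM recommendations, and how that source treats twins cannot be seen here. A reader might infer that the guideline itself ignores multiple pregnancy, or that the trial will certainly score every woman on BMI alone; the article supports neither. What can be said is that the only limits it states depend on BMI alone and that it sets no rule for multiple pregnancies.

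**The consequences are easily overstated.** This stands. A reader might infer that women with twins will fail the endpoint whatever coaching does. No figure in the article supports that: some may stay within range, and since the endpoint is gain within a range, the added weight could also lift a woman from below the range into it. A reader might also infer that earlier delivery of twins distorts the timing of the last weight before birth. The article has no data on this, and delivery date is among the recorded covariates.

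**Including all pregnancies is a defensible choice.** It is, provided the endpoint is defined for everyone enrolled. As written, it is not clear that it is.

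**Conclusion.** The point holds as a small, avoidable mismatch between eligibility and the gestational-gain endpoint. Under an assumed 1-2% share of multiple pregnancies, about 2-4 of 220 women (3-5 of 264) are affected. Even if all were scored outside the range, the group difference would shrink by only 1-2% of its value, and power in the illustration would fall by about 0.7 to 1.5 percentage points (84.8% to 84.1% or 83.3%).

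A reader might infer a biased comparison, or take the 2.7-point shift as the expected effect. Neither follows. Randomisation spreads these women over both arms, so the result is slight dilution or chance imbalance, and the 2.7 points describe a selected worst case. The 12-month BMI outcome that sets the sample size is hardly touched, because fetal weight is no longer present by then.

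The textual part of the finding is secure. Its size rests wholly on the assumed share and on the illustrative proportions. It is a low-priority improvement.

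**What to change.** Add singleton pregnancy to the eligibility criteria in the Participants section and in the Methods/Design part of the abstract, confirmed from the maternity record before randomisation. The baseline assessment at 14-16 weeks already precedes allocation, so no extra visit is needed, and because the restriction applies before allocation it does not conflict with the intention-to-treat commitment. The cost is one line of text, a check of the record, about 1-2% fewer eligible women under the same assumption, and no conclusion about multiple pregnancies, which a handful of cases could not support anyway.

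If multiple pregnancies are to stay in, state before randomisation begins that the IOM-range endpoint is analysed in women with a singleton pregnancy at baseline. Reconcile that explicitly with the Analyses section's commitment to analyse all participants in their allocated condition, for example by saying that the restriction rests on a baseline characteristic, applies equally to both arms and concerns this endpoint only.

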Since January 2010, seven additional intervention studies have been published [38-44]. The weight status of women targeted (BMI category) and the guidelines used to determine excessive GWG varied between studies. One intervention referred to guidelines recommended by the Swedish Births Registry (weight gain of 6 kg or less for all women) [39] while another did not refer to GWG guidelines at all [38]. A majority of studies included nutritional and/or physical activity behavior components as part of the intervention program [38-42,44] and four of the six interventions included a psychological component in the form of counseling or support [38,39,41,43]. A majority of the seven studies found positive effects of the intervention on the restriction of GWG [39,41-43] but results were obtained for women in different BMI categories. For example, GWG was restricted amongst normal weight women but not overweight or obese women [43], in obese women with a BMI greater than 35 kg/m^2 ^(compared to women with a BMI between 30 kg/m^2 ^and 35 kg/m^2^) [39] and in less than half of overweight or obese women (31%) [42]. Further, one study reclassified obese women (BMI > 30 kg/m^2^) as overweight and found no effect of an exercise intervention on GWG, when comparing normal/overweight women to controls using intention-to-treat analyses [44]. Only one adequately powered randomized controlled trial (RCT) [43] examined the effectiveness of an intervention to reduce excessive GWG among normal weight, overweight and obese women. Significant effects were not found for the intervention in restricting GWG in overweight or obese women according to US IOM (1990) guidelines [45], however significant effects were found for normal weight women. Further, a greater percentage of women across all weight categories reached at or below their preconception weight six months after the birth of their baby [43].

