The recent literature reflects the findings of the review by [name] et al. [26] that GWG was reduced only in some populations, and often not according to those levels recommended by the US IOM [8,45]. Furthermore, similar limitations to those present in previously reviewed interventions continue to be evident. The effect of the intervention on postpartum weight retention was not evaluated in three studies [38,39,41], and in one study intervention women were compared to an historical control group [40] and another did not refer to a control group at all [39]. Importantly, none of the recent interventions incorporated psychologically-based components of behavior change: only targeting behavior change associated with diet and physical activity. The current study addresses this gap.

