### Analyses

We will adhere to 'intention-to-treat' principles following CONSORT Statement guidelines to prevent introduction of systematic bias [48]. As such, baseline data will be secured prior to treatment allocation, missing values will be scrutinized to check for non-random distribution and primary analyses will be executed twice: once using observed data, and once using multiple imputation under multivariate normal assumptions using methods given by Schaffer [65], so that all participants will be analyzed in their allocated condition. Analyses of covariance (with "other relevant variables" from above as covariates) will test the between group differences in the primary and secondary outcomes at each assessment time point and across time points. The confounder-adjusted analysis of the proportion of women returning to pre-pregnancy weight at 12 months post birth in each group will be tested using a logistic regression model. The second hypothesis will be tested using hierarchical regressions and path analysis. In addition, to further clarify the direction of effects between two variables across multiple time points, cross-lagged panel analyses will be conducted, e.g., to determine whether the level of maternal activity/depressive symptoms is a cause or consequence of higher BMI. Finally, the interview transcripts will be analyzed using elements of phenomenology and thematic content analysis to determine barriers to adopting healthy behaviors for weight management and the support or resources that women find most useful in achieving their gestational weight gain/postpartum weight loss goals [25,66].

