## Discussion

With approximately 50% of Australian adult women of childbearing age being overweight or obese [67], the impact of pregnancy on women's weight status cannot be ignored [37]. Despite the puerperal period being a time of increased risk for both mother and child, it is also a time of unique opportunity, since pregnant women have frequent interactions with the health care system and may be especially receptive to behavior change recommendations, as evidenced by campaigns for smoking cessation in pregnancy [20]. Promoting healthy weight management around a given pregnancy is likely to favorably influence a woman's health entering her succeeding pregnancies, thus improving the health of not only her index pregnancy, but also subsequent children [68].

Our study responds to the urgent need to design effective interventions in pregnancy to prevent excessive gestational weight gain and postpartum weight retention [69]. To date, no intervention has been published that has targeted behavioral changes in relation to eating and physical activity as well as changes in psychological factors such as motivation, confidence, mood, and body image concerns, with the aim of preventing excessive gestational weight gain and 12-month postpartum weight retention. Our pregnancy HC Intervention is, therefore, novel and innovative. Moreover, it is unique in its application of health coaching principles and strategies to the life stage of pregnancy, that have been successful in instigating behavioral changes, in relation to chronic diseases including obesity, at other life stages. Our HC Intervention has been designed to be easily adopted by health professionals who work with pregnant women, such as obstetricians, midwives, GPs, and health psychologists. We additionally hypothesize that this intervention will provide a cost-effective approach to prevention of excessive gestational weight gain.

We expect the information obtained from this trial will be used to inform gestational and postpartum health practices and develop public health policies in relation to the prevention of excessive weight gain in pregnancy and weight retention post birth.

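### As described, neither the allocation blocks nor the named covariates use pre-pregnancy or baseline BMI, although the primary outcome is BMI and BMI category sets the weight-gain limits

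*Protocol article*

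**What the plan says.** **Allocation.** Participants states: "A coded, double-blinded, variable-length permuted blocks randomized treatment allocation schedule, produced by computer algorithm, will be used". Power, sample size, and retention describes permuted blocks again, more briefly. Neither description names a stratification factor.

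**Analysis.** Analyses of covariance "will test the between group differences in the primary and secondary outcomes at each assessment time point and across time points". Their covariates are given by reference to the section Other relevant variables. That list is open-ended; it names parity, socioeconomic status, social support and others, but not pre-pregnancy or baseline BMI. A confounder-adjusted logistic model is planned for return to pre-pregnancy weight. No analysis is described in which the arm effect varies with BMI.

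**The role of BMI.** The Power section names maternal BMI as the primary outcome and aims to "detect a clinically relevant difference in BMI of 0.8" kg/m² at 12 months postpartum. The Background gives IOM gain limits that differ for normal-weight, overweight and obese women, and lists high pre-pregnancy BMI among the determinants of excess gain. Eligibility starts above a BMI of 18.5 with no upper limit. Pre-pregnancy BMI (from self-reported weight) and measured BMI are both collected at the baseline visit, before allocation.

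**Earlier evidence.** Of the one adequately powered trial across these BMI categories, the Background reports that "GWG was restricted amongst normal weight women but not overweight or obese women".

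**The concern.** Pre-pregnancy or baseline BMI is likely to be the strongest predictor of BMI at 12 months, and it decides which gain limits apply to each woman. A trial that has this value before allocation would normally use it twice: to balance the arms, and as a covariate. As described, this plan does neither. At stake is precision: chance differences in BMI mix between the arms pass into the 12-month comparison and into the proportion within IOM limits, and the standard error is larger than it needs to be.

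A second, smaller issue is interpretation. The plan's own review reports effects that differed by BMI category, and a single pooled estimate cannot show in which categories coaching works.

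**Working it through.** **Inputs.** From the Power section: difference 0.8 kg/m², "a standard deviation of 2 kg/m^2^, is 110 women per group", "with 80% power at *α *= 0.05". I take the test as two-sided, which is not stated. The share overweight or obese is assumed to be 50%, borrowed from the Discussion's figure of "approximately 50% of Australian adult women of childbearing age being overweight or obese"; the article gives no figure for the trial population.

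1. **The plan's own figure.** n per arm = 2 × (1.960 + 0.842)² × 2² / 0.8² = 98.1, so 99 (100 with the t-test). The stated 110 does not reproduce, but it errs on the safe side. At 110 per arm the standard error is 2 × √(2/110) = 0.270, and power is Φ(0.8/0.270 − 1.96) = 84%. I use 110 analysed per arm below.

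2. **Chance imbalance without strata.** SD of the between-arm difference in the share overweight or obese = √(2 × 0.5 × 0.5 / 110) = 0.067, or 6.7 points. The 95% range is 1.96 × 6.7 ≈ ±13 points, and the chance of a gap of 10 points or more is about 14%. If 132 per arm are randomised, as the Power section also says, the SD is √(0.5/132) = 6.2 points (±12). For a category holding 30% or 20% of women, with 110 per arm, it is 6.2 or 5.4 points.

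3. **What that does to unadjusted 12-month BMI.** The documents give no BMI gap between women below 25 and women at 25 or above, so I assume 5 to 8 kg/m². A one-SD imbalance moves the unadjusted difference by 0.067 × 5 = 0.34 to 0.067 × 8 = 0.54. At the edge of the 95% range it moves by 0.13 × 5 ≈ 0.7 to 0.13 × 8 ≈ 1.1, against a target of 0.8.

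4. **The same point as a loss of precision.** With a 50/50 split, a gap g adds g²/4 to the variance: 6.25 for g = 5 and 16 for g = 8. If the plan's SD of 2 is the spread within BMI category, the unadjusted SD is √(4 + 6.25) = 3.2 to √(4 + 16) = 4.5. Power at 110 per arm falls from 84% to 46% (g = 5) or 26% (g = 8). Under these assumptions an SD of 2 is reached only in an analysis that adjusts for BMI.

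5. **What the data can say by BMI.** With 55 per arm in each stratum, the 95% CI half-width is 1.96 × 2 × √(2/55) = 0.75 kg/m². The standard error of the difference in effect between strata is 2 × √(4/55) = 0.54. Power for a 0.8 difference in effect is Φ(0.8/0.54 − 1.96) = 32%, and the difference detectable with 80% power is 0.54 × 2.80 = 1.51. With a 30/70 or 20/80 split, power is 27% or 22%.

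**The case against.** - **This is a condensed article.** Strata and subgroup analyses may be in a full protocol or SAP that is not shown. That stands: one can say only that the article does not describe them. But the article does commit to an allocation method and to a source for the covariates, and both can be improved as stated.

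- **Analysis of covariance usually implies adjustment for the baseline outcome.** The Power section justifies its SD by objective weighing at baseline and 12 months, so the authors may have intended this. The covariates that the Analyses section actually points to do not include it. The list is open, so naming BMI would be a clarification and not a reversal.

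- **Imbalance is chance, and the error rate of the test allows for it.** Correct. Unstratified allocation does not bias the pooled effect and does not prevent an interaction analysis. Adjustment would remove most of the noise; strata add a smaller gain on top.

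- **The pattern in earlier trials is inconsistent.** It is: the Background lists effects in normal-weight, overweight, obese or low-income women, or in none, and one study found an effect only above a BMI of 35. A split at 25 also pools overweight and obese women, whose IOM limits differ. So no modifier is established, and the analysis by BMI can only be exploratory.

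- **Two stronger readings are not supported.** A reader might infer that a pooled analysis repeats the gap that the study says it will close. The review does say that "GWG was reduced only in some populations", but the gap it says the study addresses is the absence of psychologically based components. A reader might also infer that the plan claims effectiveness in every BMI category; Specific aim 1 compares the two arms overall and makes no such claim.

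**Conclusion.** The point holds as one of efficiency, not validity. The article describes blocks without BMI strata and a covariate list that does not name BMI, for a trial whose primary outcome is BMI and whose gain endpoint is defined by BMI category. The resulting imbalance has an SD of 6.7 points (about ±13), given 110 per arm and an assumed 50% overweight or obese. The cost on 12-month BMI depends on a category gap that the documents do not give. At 5 to 8 kg/m², leaving BMI out altogether would be serious for power; naming it as a covariate largely removes the problem.

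It might also be inferred that the trial is underpowered because the effect could be confined to one half of the women. The pooled effect would then be 0.5 × 0.8 = 0.4, with 32% power, but this assumes no effect in the other half, for which the documents give no basis. Estimates by BMI are worth reporting because earlier effects differed by category, but at ±0.75 against a target of 0.8 they cannot settle where the intervention works.

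**What to change.** 1. Run the variable-length permuted blocks within two pre-pregnancy BMI strata (below 25; 25 or above). The value is collected before allocation, so no new data are needed.
2. Name continuous pre-pregnancy or baseline BMI, together with the stratum, as covariates in the analyses of covariance and the logistic models, including the model used for gain within IOM limits. This is the more important change, and it is worth making even if allocation can no longer be altered.
3. Report the arm effect with its 95% CI in each stratum, and pre-specify one arm-by-BMI term, labelled exploratory and outside the confirmatory tests.

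The cost is a slightly more complex allocation list, a few model terms and imprecise stratum estimates. No additional women are needed.
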